### Interim analyses {21b}

No formal interim analysis is planned for the study outside of the reports compiled and presented to the IDMC. The reports will cover both safety and potential efficacy of study treatment. The primary analysis, comparing time to viral rebound between placebo and dual bNAbs, will be carried out once Stage 1 is complete. A second set of analysis exploring arm B exclusively will be carried out upon completion of Stage 2.

### Methods for additional analyses (e.g. subgroup analyses) {20b}

Alongside the intention-to-treat analysis a per-protocol (PP) analysis will be carried out for some of the secondary outcome measures where participants that have withdrawn/lost-to-follow-up may potentially bias results. In addition to this, sensitivity analysis will be run on outcomes where protocol deviations may occur. These include investigations regarding missing data, and for the early restart of ART. Further details are provided within the SAP.

### Methods in analysis to handle protocol non-adherence and any statistical methods to handle missing data {20c}

There is a possibility that a small proportion of participants will be affected by COVID-19, an intercurrent event, and will need to restart ART before reaching the primary endpoint. This might affect the power, diluting the treatment effect. Other participants may also elect to restart ART before concluding follow-up without experiencing a viral rebound event. We expect this proportion to be very small and to stay within the 10% assumption used within the power calculation, but it will be monitored by trial oversight committees and sample size will be adjusted if needed. For these cases, under most scenarios censoring at time of ART restart will naturally handle missing outcome data. However, based on the pattern and extent of missingness, if appropriate, we will explore the effect of alternative missing data assumptions within sensitivity analysis using a multiple imputation approach. Further details of which will be included within the Statistical Analysis Plan.

### Plans to give access to the full protocol, participant level-data, and statistical code {31c}

Information concerning the study, patent applications, processes, scientific data, or other pertinent information is confidential and remains the property of the Sponsor. The investigator may use this information for the purposes of the study only.

The study protocol is published in this manuscript and will also be available via the clinicaltrials.gov registry. Statistical analysis plan and informed consent form will be available on request and subject to consent from the sponsor.

It is understood by the investigator that the Sponsor will use information developed in this clinical study in connection with the development of the IMPs and, therefore, may disclose it as required to other clinical investigators and to Regulatory Authorities. In order to allow the use of the information derived from this clinical study, the investigator understands that he/she has an obligation to provide complete test results and all data developed during this study to the Sponsor.

Verbal or written discussion of results prior to study completion and full reporting should only be undertaken with written consent from the Sponsor.

Therefore, all information obtained as a result of the study will be regarded as confidential, at least until appropriate analysis and review by the investigator(s) are completed.

Permission from the Trial Management Group is necessary prior to disclosing any information relative to this study outside of the Trial Steering Committee. Any request by site investigators or other collaborators to access the study dataset must be formally reviewed by the TSC.

A Clinical Study Report summarising the study results will be prepared and submitted to the REC within a year of the end of study. The results will also be submitted to the EudraCT results database in accordance with regulatory requirements.

#### Sub-studies

Investigators planning sub-studies may submit their proposals for consideration by the TSC, IDMC, and TMG. Planned or current sub-studies within the RIO trial includes a qualitative sub-study investigating the participant experience within the RIO study, and a sub-study for the collection of rectal biopsies in RIO participants, to investigate the pharmacokinetics of bNAbs and their impact on the gut HIV reservoir and mucosal immunity.

## Oversight and monitoring

### Composition of the coordinating centre and trial steering committee {5d}

A Trial Steering Committee (TSC) will be convened including as a minimum an independent Chair, independent clinician, the CI, and Trial Manager. The TSC charter is included in Supplement file 2. The role of the TSC is to provide overall supervision of trial conduct and progress. The TSC will meet approximately 6-monthly throughout the duration of the trial. Details of membership, responsibilities, and frequency of meetings will be defined in a separate Charter.

A Trial Management Group (TMG) will be convened including the CI, co-investigators and key collaborators, community representative, trial statistician, and trial manager. The TMG will be responsible for day-to-day conduct of the trial and operational issues. Details of membership, responsibilities, and frequency of meetings will be defined in separate Terms of Reference.

### Composition of the data monitoring committee, its role and reporting structure {21a}

A fully IDMC will be set up to monitor progress, participant safety, and any ethical issues involved in this trial. They will review trial progress, recruitment rates, and safety data. A separate IDMC Charter will be drawn up defining their responsibilities, frequency of meetings, and reporting to the TSC (Supplement file 3). Meetings will be approximately 6-monthly.

The statistician will analyse interim data for IDMC meetings and act as data manager, in raising and resolving data queries with participating sites, via the Trial Manager. Closed IDMC reports will include recruitment, randomisation balance and stratification effectiveness, baseline characteristics, unblinding, withdrawals, compliance, concomitant medications, efficacy, mediators, and adverse events. Open IDMC and TSC reports will be provided without outcome or arm information.

There are no statistical criteria (stopping rules) defined for termination of the RIO trial. The IDMC Charter will define procedures for early termination of the study due to safety, should this be required.

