## Assignment of interventions: Blinding

### Who will be blinded {17a}

Apart from ICRF research staff who will administer either the IMP or placebo, all trial participants, care providers, outcomes assessors, and data analysts will be blinded to the study arm allocation of each participant for the duration of Stage 1 of the trial.

ICRF research staff will be blinded to outcomes collection and analysis.

The Independent Data Monitoring Committee (IDMC) and study statistician preparing the IDMC report will require access to fully unblinded data.

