#### Unblinding for statistical analysis

When performing safety and interim analyses, the integrity of trial blind should be maintained, with the exception of the IDMC who will have access to fully unblinded data. The Study Statistician preparing the IDMC report will also require access to fully unblinded data in order to prepare the report. Unblinding in these cases should take place in accordance with Imperial Clinical Trials Unit (ICTU) Standard Operating Procedures (SOP) and documented accordingly.

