## Statistical methods

### Statistical methods for primary and secondary outcomes {20a}

Statistical methods for analysis of the study endpoints are described below. A separate detailed Statistical Analysis Plan (SAP) will be prepared and finalised prior to database lock. This will contain the rationale for the methods chosen and the assessment of their assumptions. It will include pre-specifying the handling of covariates and missing data and per protocol analyses. The per-protocol (PP) population will remove participants that are non-compliant in their treatment regimen. This will consist of the following: any participant that fails to successfully receive infusion (placebo or bNAb), any participant that fails to adhere to ATI, as established by detection of ART within blood sample, any participant that is lost-to-follow-up/withdrawn, any participant that fails to either (a) complete the 36-week follow-up period or (b) register viral rebound with the EAC. ITT population will include all participants randomised into the study according to their allocated arm at randomisation, regardless of treatment received. Changes to the plan will be re-approved by trial oversight committees.

Any deviations from the SAP will be documented and signed off by the statisticians and CI and filed in the statistics section of the Trial Master File (TMF) which will be merged with the main TMF at the end of the study.

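### The statistician who prepares unblinded efficacy reports for the IDMC also runs site data queries, and the SAP may be finalised as late as database lock

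*Protocol article*

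**What the plan says.** All references are to the protocol article.

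- **Combined role.** Section {21a} states: "The statistician will analyse interim data for IDMC meetings and act as data manager, in raising and resolving data queries with participating sites". It adds that these queries go through the Trial Manager.
- **Access.** The section on unblinding for statistical analysis states: "The Study Statistician preparing the IDMC report will also require access to fully unblinded data in order to prepare the report". Section {17a} says the same.
- **Content of the reports.** Section {21b}: "The reports will cover both safety and potential efficacy of study treatment". Section {21a} lists among the contents of the closed reports "unblinding, withdrawals, compliance, concomitant medications, efficacy, mediators, and adverse events". IDMC meetings are to be held about every six months.
- **Blinding rule.** Section {17a} says that "care providers, outcomes assessors, and data analysts will be blinded to the study arm allocation" for the duration of Stage 1. Section {16c} names the study monitor and the clinical research facility team as the sole unblinded parties.
- **SAP timing.** Section {20a}: "A separate detailed Statistical Analysis Plan (SAP) will be prepared and finalised prior to database lock". The same part of the article leaves covariates, missing data and the censoring definition for the primary Cox model to the SAP.

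**The concern.** Raising and resolving queries involves judgement: which entries look implausible, which are pursued, and when an answer is accepted. If the person making those decisions knows the arm and has seen the comparative results, scrutiny can differ between arms without anyone intending it. In a double-blind trial this work normally sits with people who have not seen allocation.

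The SAP deadline raises a similar question about analysis rules. A plan completed shortly before lock, after closed reports have been issued, cannot by its date alone show that its remaining choices were made without knowledge of the results. With 72 participants, a few altered start or censoring dates could matter.

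**Working it through.** The plan gives no figure to reproduce. The check compares the texts and adds one short timing calculation.

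1. **Is it the same role?** Section {21a} joins the interim analysis and the data-manager task in one sentence about one statistician. Section {17a} and the section on unblinding for statistical analysis give unblinded access to the statistician who prepares the IDMC report. Analysing interim data for the IDMC and preparing its report are, on a natural reading, one job. The overlap is therefore stated by the article, not inferred from silence.

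2. **Does the access include efficacy?** Yes, under both {21b} and {21a}.

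3. **Do the blinding statements allow for it?** Section {17a} sets a general rule and then an exception for the IDMC and its statistician. The exception is tied to the report and does not mention site queries. Section {16c} fits less well. Its closed list of unblinded parties leaves no place for the statistician. It also refers to one study monitor, whereas section {23} separates a blinded monitor, who compares source data with the eCRF, from an unblinded monitor confined to IMP supply and pharmacy matters.

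4. **Which records could arm-aware querying reach?**
   - *Rebound date:* based on laboratory viral loads and set by an independent committee blinded to arm ({20a}). Largely protected.
   - *ART stop date:* time 0 for the primary endpoint (section on antiretroviral treatment interruption). Open to query.
   - *ART restart date:* the censoring time for early restarters whom the committee judges not to be endpoints ({20a}). The committee decides endpoint status, but the date comes from site data.
   - *Adherence and per-protocol status:* rest on infusion receipt, ART detection in blood and completeness of follow-up ({20a}). Section {20b} applies the per-protocol analysis to some secondary outcomes only.
   - *Adverse events:* outside the adjudication committee's described remit.

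5. **Can the SAP deadline fall after an unblinded efficacy report?** Six-monthly meetings are about 52 / 2 = 26 weeks apart. The primary window is 36 weeks, and 36 > 26. If the approximate schedule holds and any late-enrolled participant is followed to week 36, at least one meeting falls inside that participant's window, and so before lock. The total number of reports cannot be derived, because the article gives no recruitment period.

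6. **What is left for the SAP to decide?** The article already fixes the ITT and per-protocol populations, Cox regression, two-sided 5% testing and censoring at ART restart for non-endpoints ({20a}, {20c}). Still open are the remaining censoring detail, covariates and missing-data handling. Under {20c}, multiple imputation is a sensitivity analysis whose use depends on the missingness observed.

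**The case against.** The case on the other side has substance. Queries pass through the Trial Manager. Investigators sign off eCRF data and changes leave an audit trail. A blinded monitor checks source data independently. The adjudication committee is blinded and also reviews every ART restart before rebound. Unblinding follows the trials unit's SOPs, and an IDMC Charter exists. Neither is shown, and either might describe a firewall.

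These safeguards narrow the exposure but do not remove it. The Trial Manager relays queries; nothing says that the selection of queries is blinded. An audit trail records what changed, not what was left unchallenged. The article itself assigns the combined role, so this is not detail lost in condensing.

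Four stronger readings are tempting, and the document does not support them:

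- *That the unblinded statistician writes the SAP.* No section names its author. Section {20a} refers to statisticians in the plural when describing sign-off of deviations, and the statistician preparing the IDMC report may be a different person. Shared authorship is neither stated nor excluded.
- *That section {17a} contradicts itself on data analysts.* It gives a rule and then its exception. The statement that does not fit is the one in {16c}.
- *That the primary comparison is biased.* The adjudication safeguards and the rules already fixed leave only a narrow route, and no actual bias is shown.
- *That planned unblinding at rebound measures the problem.* On the sample-size rates, 36 × 0.90 + 36 × 0.55 = 52.2 of 72 participants (72.5%) would rebound by week 36 and be unblinded. That counts participants and local teams unblinded by design. It does not measure what the statistician knows.

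Section {20a} also requires oversight committees to re-approve SAP changes. That covers changes to the plan, not its first finalisation.

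**Conclusion.** The point holds in two parts, at moderate severity.

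First, the article gives data-query work to the statistician who holds arm-level efficacy data, and section {16c} does not fit with that statistician's access. The exposure is mainly in ART stop and restart dates, adherence and per-protocol status, and adverse events; rebound dates are largely protected. This rests on reading the statistician in {21a} as the one described in {17a}.

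Second, the SAP deadline allows remaining analysis detail to be settled after unblinded efficacy reports have been issued. Whether anyone who has seen those reports takes part is unknown. Section {20a} sets only a latest date, and the actual sign-off may have been earlier.

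No numerical size can be attached to either part. The case for change is that the arrangement is avoidable at little cost.

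**What to change.** 1. **Section {21a}:** move the raising and resolving of queries to existing blinded staff, namely the Trial Manager and the blinded monitor of section {23}. Limit the unblinded statistician to preparing IDMC reports. The article does not expressly list the Trial Manager as blinded, so this should be stated.
2. **Sections {16c}, {17a}, {21a} and unblinding for statistical analysis:** reconcile them into one list of who is unblinded, to what and for what purpose, specifying which monitor is meant.
3. **Section {20a}:** require SAP sign-off before the first closed report with efficacy by arm. If that has passed, allow sign-off and later changes only by staff documented as blinded to arm-level results.

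The cost is some added query work for the Trial Manager and monitor and an earlier SAP deadline. No new post is needed. One limit remains: individual allocations become known locally after confirmed rebound, so the change protects query decisions from comparative results and from the allocation of participants not yet unblinded, but not from every known allocation.

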#### Endpoint Adjudication Committee

An independent panel of experts will be convened to review all viral rebound reports and confirm that these meet the trial definition for viral rebound. Copies of the viral rebound reports will be provided to the panel, along with redacted copies of any applicable lab reports and the outcome of the review will be recorded on the eCRF. The panel will agree their terms of reference at the start of the trial and will meet on a 6-monthly basis, or as required over the course of the trial.

Immunological symptoms listed below are possible with administration of a monoclonal antibody and will be considered AEs of interest. Potential allergic-type reactions during and immediately following the administration of 10-1074-LS and 3BNC117-LS will be carefully monitored.
Constitutional symptoms, e.g. fever, change in blood pressure, rigours/chills.Injection site reactions/extravasation changes, pruritis, urticaria, erythema, desquamation, ulceration.Serum sickness like syndromes as evidenced by fever, rash, arthralgia, arthritis, nephritis.Deposition of immune complexes in the kidneys leading to renal insufficiency.Anaphylaxis; adult respiratory distress syndrome, bronchospasm, or wheezingCytokine release syndrome

Suspected unexpected serious adverse reactions (SUSARs) are defined as a SAR judged related to any dose of study drug administered, and not consistent with the applicable to the product information as set out in the IB for the investigational medicinal products. SUSARs should be notified to the appropriate regulatory authority, relevant REC, and the sponsor in accordance with regulatory requirements. SUSARs which are fatal or life-threatening will be reported not later than 7 days after becoming aware of the SAE. Any additional relevant information will be sent within 8 days of the report. Other non-fatal or life-threatening SUSAR will be reported within 15 days. Follow-up of participants who have experienced a SUSAR should continue until recovery is complete or the condition has stabilised. SUSAR reports should be unblinded prior to submission if required by national regulatory requirements.

Annual safety reports will be submitted to the sponsor, the ethics committee, and regulatory authority in accordance with regulatory requirements.

If a participant or their partner becomes pregnant while taking part in the trial where the foetus could have been exposed to an IMP, the investigator must ensure the participant and their healthcare professional are aware that follow-up information is reported on the outcome of the pregnancy. Each pregnancy will be reported to the ICTU within 24 h of learning of its occurrence. Any SAE experienced during the pregnancy and unrelated to the pregnancy must be reported on a SAE form. The pregnancy should be followed up to determine outcome, including spontaneous or voluntary termination, details of the birth, and the presence or absence of any birth defects, congenital abnormalities, or maternal and/or newborn complications. Pregnancy follow-up should be recorded on the same form and should include an assessment of the possible relationship to the investigational treatment.

If any urgent safety measures are taken, the CI/sponsor shall immediately and no later than 3 days from the date the measures are taken, give written notice to the MHRA and relevant REC of the measures taken and the circumstances giving rise to those measures.

### Frequency and plans for auditing trial conduct {23}

The study will be monitored periodically by trial monitors to assess the progress of the study, verify adherence to the protocol, GCP guidelines, and other national/international requirements and to review the completeness, accuracy, and consistency of the data.

The trial will require two separate monitoring roles:

(a) Blinded trial monitor responsible for reviewing informed consent, trial data (comparison of source data against eCRF), review and oversight of laboratory samples

(b) Unblinded trial monitor responsible for review of IMP supply and pharmacy aspects

A study-specific risk assessment will be performed prior to the start of the study to assign a risk category of ‘low’, ‘medium’, or ‘high’ to the trial. Risk assessment will be carried out by the ICTU Quality Assurance Manager in collaboration with the Study Manager and the result will be used to guide the monitoring plan. The risk assessment will consider all aspects of the study and will be updated as required during the course of the study.

Monitoring procedures and requirements will be documented in a monitoring plan, developed in accordance with the risk assessment.

Quality control will be performed according to ICTU internal procedures. The trial may be audited by a Quality Assurance representative of the Sponsor and/or ICTU. All necessary data and documents will be made available for inspection.

The study may be subject to inspection and audit by regulatory bodies to ensure adherence to GCP and the NHS Research Governance Framework for Health and Social Care (2nd Edition).

### Plans for communicating important protocol amendments to relevant parties (e.g. trial participants, ethical committees) {25}

Prior to the shipment of IMP and the enrolment of participant, the REC must provide written approval of the following: the conduct of the study at named sites, the protocol and any amendments, the Participant Information Sheet and Consent Form, any other written information that will be provided to the participants, any advertisements that will be used, and details of any participant compensation.

Proposed amendments to the protocol and aforementioned documents must be submitted to the REC for approval as instructed by the Sponsor. Amendments requiring REC approval may be implemented only after a copy of the REC’s approval letter has been obtained.

Amendments that are intended to eliminate an apparent immediate hazard to participants may be implemented prior to receiving Sponsor or REC approval. However, in this case, approval must be obtained as soon as possible after implementation.

The trial team, in collaboration with the Sponsor, will assess whether a proposed amendment is substantial or non-substantial. For each proposed amendment, a revised version of the protocol will be prepared using tracked changes, a new version number assigned, and the revised document will be reviewed and approved by Protocol Development Group and Sponsor prior to submission to the REC and Health Research Authority (HRA). The amended protocol will be sent to participating sites for local approval to be granted and the approved version will be shared with all staff involved in the trial.

